At the end of the study period, both baseline RISE and longitudinal changes of RISE will be tested as predictors of mortality. Other individual variables will also be tested as predictors of mortality, including age at the time of diagnosis, time between onset of symptoms and diagnosis (months), gender, body mass index, smoking history (pack-years), FVC, DLCO, 6MWD (meters and % predicted), desaturation during 6-min walk test, HRCT visual fibrosis score at the time of diagnosis, and other multi-dimensional scores (GAP, CPI, MRSS). In the validation cohort, we will seek to confirm and validate results obtained in the development cohort.

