### Primary endpoint

Three-year, LTx-free survival from the time of diagnosis, measured as the time between diagnosis and death from any cause, or LTx. Once they receive a LTx, patients will be censored. Since mortality and LTx are competing events, a Fine-Gray competing risk regression analysis will be used. Please refer to the statistics section for details.

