### Secondary endpoints

Comparative analysis of RISE as predictor of LTx-free survival in subgroups stratified by age; gender; baseline lung function; baseline 6MWD; baseline extent of fibrosis on HRCT; time between onset of symptoms and diagnosis; presence of APH; presence of concomitant emphysema; presence of comorbidities (COPD, CAD, LHD, SA); participating site.Clinical progression, as a predictor of mortality, defined as either: absolute decline of FVC >10% pred; decline of 6-min walk distance >50 m; hospitalization for respiratory causes; LTx assessment; or death.Incidence of AEs of IPF and its predictors, if any.Incidence of hospitalizations due to respiratory causes and its predictors, if any.LTx-free survival, incidence of AEs, incidence of hospitalizations, and time to progression of patients with HRCT pattern definite/probable for UIP vs. patients with indeterminate/inconsistent pattern. In this subanalysis, 2 groups of patients matched for age, gender, BMI, and extent of fibrosis at the time of diagnosis will be considered.LTx-free survival, incidence of AEs, incidence of hospitalizations, and time to progression of patients with autoimmune markers (although not meeting criteria for interstitial pneumonia with autoimmune features [23] versus those without. In this subanalysis, 2 groups of patients matched for age, gender, BMI and extent of fibrosis at the time of diagnosis will be considered.LTx-free survival, incidence of AEs, incidence of hospitalizations and time to progression of patients with concomitant emphysema versus those without. In this subanalysis, 2 groups of patients matched for age, gender, BMI and extent of fibrosis at the time of diagnosis will be considered.LTx-free survival, incidence of AEs, incidence of hospitalizations and time to progression of patients treated with pirfenidone versus patients treated with nintedanib. In this subanalysis, 2 groups of patients matched for age, gender, BMI and extent of fibrosis at the time of diagnosis will be considered.LTx-free survival, incidence of AEs, incidence of hospitalizations and time to progression of patients whose therapy was switched (from pirfenidone to nintedanib and viceversa). In this subanalysis, 2 groups of patients matched for age, gender, BMI and extent of fibrosis at the time of diagnosis will be considered.6MWD m versus % pred as predictors of mortality.Survival, incidence of AEs and time to progression on the LTx waitlist of listed patients.Time to progression in patients with initially non-clinically significant disease.Long-term follow-up (beyond 3 years) of patients who are still alive without a LTx, until required recruitment is completed. This will include LTx-free survival, incidence of AEs, incidence of hospitalizations and time to progression.

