### Statistical analysis and sample size calculation

The distribution of variables considered will be analysed with Kolmogorov–Smirnov test. Interobserver variability among chest radiologists and lung pathologists will be assessed with Weighted kappa coefficients [29]. Survivors and non-survivors will be compared by using the unpaired t-test, or, for not normally distribute variables, with the Mann–Whitney U-test. To rule out multicollinearity and demonstrate that included variables are truly independent, variance inflation factors of the RISE components will be calculated [30]. Receiver operating characteristics analysis will be used to identify the most accurate cut-off values for each variable to predict endpoints. Multivariate analysis of significant predictors of endpoints will be conducted with the Cox proportional hazard model. Results will be summarized as hazard ratios. Once patients are listed for LTx, death and LTx become competing events. To account for the competing risks of LTx and death in the population of patients undergoing LTx assessment, the Fine-Gray competing risk regression model [31] will be used. This will identify variables significantly predicting independent survival status and results will be summarized as subdistribution hazard ratios. These represent the relative risk of dying prior to LTx. Survival will be further evaluated using Kaplan–Meier curves and the log-rank test. Sample size calculation for an observational, cohort study was conducted using the methodology described by Wang and Ji [32], with the assistance of a statistician. Using available, preliminary data on 109 patients, dropout rate, ratio of low RISE to high RISE, and mortality rates in low RISE and high RISE subgroups were determined. With a power (probability of detecting a real effect) of 90%, and with a conservative approach, a sample size of 125 patients for each cohort was determined to be required.

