## Discussion

IPF is a condition associated with a poor prognosis [2–4], but clinical deterioration occurs with rather difficult to predict patterns. Many deaths in IPF occur due to subacute respiratory deterioration [4], with a slow decline in lung function. Nevertheless, approximately 30% of the patients die because of AEs, while infection, pulmonary embolism, heart disease, and lung carcinoma have a significant impact on the evolution of the disease in individuals affected by IPF as well [4]. Anti-fibrotic agents pirfenidone and nintedanib have shown to slow the disease course [6, 33], but LTx remains the only definitive treatment for this disease, associated with significantly improved survival [34].

In this context, clinical decision making on therapy start and switch has a direct impact on survival. It is also equally important not to miss the LTx window, when patients are still eligible for transplant. This is particularly challenging when navigating a lengthy assessment process with a condition that can be rapidly progressive. Not surprisingly, LTx waitlist mortality is the highest among patients with IPF [35]. As a result, clinical tools able to detect clinically significant progression and predict the prognosis in individual patients are paramount in IPF.

In this observational, prospective trial, RISE will be tested as a candidate staging system for IPF to be used in day-to-day clinical decision making. RISE is designed to be straightforward, easy to obtain and repeat, inexpensive and entirely managed by the pulmonary specialist. The 3 domains captured by RISE are exertional dyspnea, exercise capacity and lung function. The prognostic independence between the 3 domains has been demonstrated [3].

As in all chronic lung diseases, IPF impacts patients’ quality the life with disabling symptoms (i.e., dyspnea and cough) and with functional impairment in everyday life. As far as dyspnea perception is concerned, several scales have been utilized. Among them, an increase of MRCDShas shown good correlation with quality-of-life impairment [36, 37] and mortality [38] in patients with IPF.

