The 6-min walk test is a well-established tool in the evaluation of chronic lung diseases, since it was demonstrated to correlate well with both quality of life [39] and post-therapeutic improvement [40], and to provide useful data for the prescription of ambulatory oxygen in ILDs [41]. Importantly, 6MWD was shown to also predict mortality in IPF: a 24-week decline of greater than 50 m [42] and the presence of desaturation during the test in patients with UIP [43] are both associated with an increase in risk of death at 1 year.

FVC decline significantly correlates with mortality in patients affected by IPF, even with a marginal decline of more than 5% at a 6-month interval [44]. Indeed, pirfenidone and nintedanib were approved for clinical use based on the data on FVC decline. FVC alone, however, has significant limitations in detecting progression of disease, as pointed out by several studies [6, 45]. The advantage of using the CPI is the combination of FVC with DLCO and FEV_1_. This index was developed against the morphologic extent of fibrosis on HRCT and considers the presence of coexisting pulmonary emphysema, which may be a confounding element in the interpretation of pulmonary function tests [15]. An improved version of the CPI was developed against the CALIPER-measured extent of fibrosis [13].

To predict the prognosis of such a complex condition as IPF, a multidimensional approach encompassing different domains is likely to better account for the severity of the disease, compared to a single variable approach [9]. A first step to identify the variables to associate in a multi-dimensional scoring system is to prove that each parameter is an independent predictor of the endpoint, and that there is no strong correlation or collinearity [30] among them. This has been proven in several studies for MRCDS, 6MWD and lung function measures [3, 8, 10], making them suitable candidates to be included in a prognostic score for IPF.

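### The matched emphysema comparison leaves out pack-years, which are recorded, so a difference between the groups could not be separated from an effect of smoking

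*Protocol article*

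**What the plan says.** The Secondary endpoints section of the protocol article lists five matched subanalyses: UIP pattern on HRCT, autoimmune markers, emphysema, pirfenidone versus nintedanib, and switch of therapy. All use the same matching variables. For emphysema, the outcomes are those "of patients with concomitant emphysema versus those without. In this subanalysis, 2 groups of patients matched for age, gender, BMI and extent of fibrosis" at diagnosis.

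Methods and design lists the variables to be tested as predictors of mortality. That list includes "gender, body mass index, smoking history (pack-years), FVC, DLCO, 6MWD (meters and % predicted" as well as age and the HRCT fibrosis score. All four matching variables are therefore on the list, and so is smoking, but smoking was not taken into the matching set.

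The survival endpoint is "measured as the time between diagnosis and death from any cause, or LTx". The Discussion states that "infection, pulmonary embolism, heart disease, and lung carcinoma have a significant impact on the evolution of the disease" in people with IPF.

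On adjustment, Statistical analysis and sample size calculation says: "Multivariate analysis of significant predictors of endpoints will be conducted with the Cox proportional hazard model". It does not connect this model to any of the matched subanalyses.

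**The concern.** Matching is meant to make the two groups comparable on things other than emphysema that could drive the outcome. A single generic set was applied to five quite different comparisons. For emphysema it omits a recorded exposure that the protocol itself treats as a possible predictor of death. The endpoint counts deaths from all causes, so any deaths linked to smoking count as events whichever disease they come through.

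If pack-years differ between the matched groups and also predict outcome, the comparison mixes two contributions and the stated method cannot separate them. At stake is the reading of one secondary result: whether IPF patients with emphysema fare differently from similar patients without it.

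**Working it through.** **Is smoking handled anywhere for this comparison?** The article gives no numerical result, effect size or sample size for the emphysema comparison, so there is no figure of its own to reproduce. The textual check is:

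- Secondary endpoints: four matching variables, smoking not among them.
- Methods and design: pack-years recorded and to be tested as a predictor of mortality.
- Statistical analysis: a general Cox model of significant predictors, not tied to the matched groups.
- Discussion: emphysema is treated as a confounder of lung function (the CPI "considers the presence of coexisting pulmonary emphysema, which may be a confounding element in the interpretation of pulmonary function tests"), but smoking is not mentioned there.

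No smoking adjustment is stated for this subanalysis.

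**Size of the bias, smoking as ever/never.** All inputs are assumptions, including the direction (more smokers in the emphysema group). Let p1 and p0 be the proportions of ever-smokers with and without emphysema after matching, and RR the mortality ratio for smoking. With no true emphysema effect, the spurious ratio is

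bias = [1 + p1(RR − 1)] / [1 + p0(RR − 1)]

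| RR | 70% vs 70% | 90% vs 60% | 95% vs 50% |
|---|---|---|---|
| 1.0 | 1.00 | 1.00 | 1.00 |
| 1.2 | 1.00 | 1.18/1.12 = 1.05 | 1.19/1.10 = 1.08 |
| 1.5 | 1.00 | 1.45/1.30 = 1.12 | 1.475/1.25 = 1.18 |
| 2.0 | 1.00 | 1.90/1.60 = 1.19 | 1.95/1.50 = 1.30 |

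**Size of the bias, smoking as pack-years.** With h the hazard ratio per 10 pack-years and d the remaining mean difference in pack-years, the spurious hazard ratio is h^(d/10). It is 1.00 if h = 1 or d = 0. Otherwise: 1.05^1 = 1.05; 1.10^2 = 1.21; 1.20^2 = 1.44. The last value needs the top of both assumed ranges (h = 1.20 and d = 20).

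**Effect on a nominal 5% test.** The article plans 125 patients per cohort, sized on low versus high RISE; pooling both gives 250. If 20% to 40% have emphysema (assumed) and each finds a match, there are 250 × 0.20 = 50 to 250 × 0.40 = 100 pairs. With 30% to 50% having an event by 3 years (assumed), events run from 2 × 50 × 0.3 = 30 to 2 × 100 × 0.5 = 100. The chance that a two-sided log-rank test rejects when emphysema has no effect, ignoring the pairing, is

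Φ(√(events/4) × ln bias − 1.96) + Φ(−√(events/4) × ln bias − 1.96)

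| Bias | 30 events | 100 events |
|---|---|---|
| 1.08 | 5.5% | 6.7% |
| 1.15 | 6.7% | 10.8% |
| 1.30 | 11.1% | 25.9% |

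These figures concern mortality or LTx-free survival. None was worked out for exacerbations, hospitalizations or progression, where the same logic applies but the inputs would differ.

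**The case against.** The strongest reply is that the comparison may be purely prognostic: do patients with emphysema do worse at the same age, gender, BMI and fibrosis extent? For that question, leaving smoking unmatched is legitimate, and adjusting for it answers a different question. This stands as far as it goes, and it is the reason to report both results rather than replace one with the other.

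A second reply is that the Cox model could include pack-years. It could, but the text does not link it to the matched groups. A variable that enters only if significant can also miss significance and still bias a comparison. A third is that an article condenses the full protocol. However, the matching set is stated here explicitly, not deferred.

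Some stronger readings are tempting, and the article does not support them:

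- *A difference will be credited to emphysema.* The Secondary endpoints section describes a group comparison and makes no causal statement.
- *Smoking is the recorded variable most likely to differ.* No smoking figures by emphysema status are given. FVC, DLCO and COPD are also recorded and unmatched, and could differ as much.
- *The whole smoking difference survives matching.* Matching on age and gender may remove part of it.
- *The abstract's claim of reproducibility in patients with emphysema is undermined.* That claim concerns RISE and rests on the separate analysis of RISE within subgroups, which involves no matching between emphysema groups.

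**Conclusion.** The point holds as a limited weakness in one secondary subanalysis. As written, the comparison is open to confounding by smoking, which the study already records. The distortion is conditional: it needs pack-years both to differ between the matched groups and to predict outcome, and the article establishes neither. Under the assumptions used, it runs from none (ratio 1.00) to about 1.3, with 1.44 only when both pack-year assumptions are at their extreme. At a bias of 1.08 the false-positive rate barely moves; at 1.30 it is roughly two to five times the nominal 5%. The primary validation of RISE and the RISE subgroup analysis by emphysema do not depend on this comparison. Making the change is desirable rather than essential.

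**What to change.** In the emphysema subanalysis, add pack-years as a covariate in the model fitted to the matched groups, and report the estimate with and without it. The unadjusted figure answers the prognostic question; the adjusted one shows how much of the difference remains at equal recorded smoking history. One added phrase is enough and no new data are needed. The cost is a slightly wider interval. Matching on pack-years is an alternative, but it may leave some never-smokers unmatched, so the covariate is preferable because it keeps every matched patient.

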## Methods and design

This is an observational, international, prospective cohort study including 2 large tertiary referral centres for interstitial lung disease (ILD) (London, Canada and Rome, Italy). The study was designed to reflect common clinical practice in IPF.

Only patients newly diagnosed with IPF based on the American Thoracic Society/European Respiratory Society (ATS/ERS) criteria [1] and local multi-disciplinary discussion (MDD) [18] at participating centres will be included in the study. As a further inclusion step, for all patients who did not undergo a surgical lung biopsy (SLB), a panel of 3 chest radiologists with ILD expertise will examine each HRCT, and patients will be included, if at least 2 out of 3 agree on a pattern of probable/definite UIP. For patients who underwent a SLB, a panel of 3 lung pathologists with ILD expertise will examine each biopsy, and patients will be included if at least 2 out of 3 agree on a pattern of probable/definite UIP.

All known causes of ILD will carefully excluded before each patient is included in the study. These include domestic, environmental, occupational, exposures; drug-induced lung toxicity; and connective tissue diseases. Comorbidities considered will include APH (only if right heart catheterization[RHC]-proven), chronic obstructive pulmonary disease (COPD), coronary artery disease (CAD), left heart dysfunction (LHD), and sleep apnea (SA).

A development cohort and a validation cohort will be included in the study. In both cohorts, at the first visit (time of diagnosis) and at each subsequent visit at 4-month intervals, for a period of 3 years, MRCDS (Table 1), pulmonary function tests (PFTs)(forced expiratory volume during the first second [FEV_1_], FVC, diffusing lung capacity for carbon monoxide [DLCO]), and 6MWD will be obtained. 6MWD % predicted will be calculated, as previously described [19]. The use of supplemental oxygen and the level of oxygen desaturation will be considered. The following events will be recorded in the study: death; LTx referral; LTx; AEs; hospitalization for respiratory causes; start, stop and switch of anti-fibrotic therapy; start of supplemental home oxygen therapy; start and stop of physiotherapy program enrolments; progression of disease (see Secondary endpoints).

**Table 1 Tab1:** MRC dyspnea score (0 to 5 scale) [20]

Grade	Description
0	I only get breathless with strenuous exercise

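### The drug-versus-drug and switch subanalyses match on four diagnosis-time variables that omit the study's own main predictors, and a clock from diagnosis adds immortal-time bias if start or switch timing differs between groups

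*Protocol article*

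**What the plan says.** Under Secondary endpoints, one subanalysis takes LTx-free survival, acute exacerbations, hospitalizations and "time to progression of patients treated with pirfenidone versus patients treated with nintedanib". The next takes the same first three outcomes and "time to progression of patients whose therapy was switched (from pirfenidone to nintedanib and viceversa"). It does not say with whom the switched patients are compared.

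Each of the paired subanalyses in that list carries the same matching rule: "2 groups of patients matched for age, gender, BMI, and extent of fibrosis at the time of diagnosis will be considered".

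The clock is defined once, under Primary endpoint: "Three-year, LTx-free survival from the time of diagnosis", "measured as the time between diagnosis and death from any cause, or LTx". The two treatment items reuse the name of this endpoint and give no other origin. Methods and design lists "start, stop and switch of anti-fibrotic therapy" among the events recorded during the study.

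The Background states that dyspnea, lung function and 6MWD predict survival independently of one another. RISE is built on those three domains.

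**The concern.** There are two separate problems.

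**Confounding.** Treatment is chosen, not allocated. The matching set contains none of the three domains that the study regards as carrying the prognosis. It is also fixed at diagnosis, whereas a switch happens later and may well be prompted by how the disease has behaved since. A difference in severity at the start or switch would then be read as a drug effect.

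**Time origin.** A switch can only come after a first drug has been started, so a patient must stay alive and untransplanted to be counted as switched. If survival is counted from diagnosis, the waiting time before the switch is credited to the switched group although no death could occur in it. A similar effect can arise between the two drugs if one tends to be started later than the other.

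The Discussion says that decisions on starting and switching therapy bear directly on survival, so readers are likely to take these comparisons as evidence on treatment.

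**Working it through.** The article gives no figure for these comparisons to reproduce. Its 125 patients per cohort refers to low versus high RISE and has no bearing here. The calculations below assume **no true effect**, so the correct ratio is always 1.00.

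**Inputs.** Follow-up of 3 years (Methods and design). Mean survival of 3 to 5 years without therapy (Background), taken as exponential; the examples in steps 1 and 2 use 4 years, so λ = 0.25 per year. Switch rates, start delays and confounder strengths are not in the article and are assumptions.

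**1. Switched versus never switched, counted from diagnosis.** Assume that 40% would switch by 3 years in the absence of death: μ = −ln(0.60)/3 = 0.1703 and κ = λ + μ = 0.4203. Per patient enrolled:

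- All deaths: 1 − e^(−0.75) = 0.5276. Deaths without a switch: (λ/κ)(1 − e^(−3κ)) = 0.4263. Deaths after a switch: 0.5276 − 0.4263 = 0.1014 (from unrounded values).
- Person-years in total: 0.5276/0.25 = 2.1105. After a switch: 0.4055. Switchers before their switch: (μ/κ²)[1 − e^(−3κ)(1 + 3κ)] = 0.3463. Never switched: 1.3587.
- From diagnosis: 0.1014/(0.4055 + 0.3463) = 0.1348 against 0.4263/1.3587 = 0.3137. **Ratio 0.43.**
- With switch as time-dependent: 0.1014/0.4055 = 0.25 against 0.4263/(1.3587 + 0.3463) = 0.25. **Ratio 1.00.**

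Over mean survival of 3 to 5 years and switching of 20% to 40%, the ratio from diagnosis is 0.43 to 0.47. A Cox simulation over wider assumptions (death hazard 0.15 to 0.25 and switch hazard 0.1 to 0.3 per year) gave hazard ratios of 0.36 to 0.51.

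**2. Pirfenidone versus nintedanib, counted from diagnosis.** Both groups must survive to their start. With start delay d, the rate from diagnosis is λ·P/(P + λd), where P = 1 − e^(−λ(3−d)).

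- Equal delays: the factors cancel. Ratio 1.00.
- Delays of 0 and 0.33 years: factors 1.000 and 0.8551. Ratio 1/0.8551 = 1.17, in favour of the drug started later. For mean survival of 3 to 5 years, a difference of about 4 months gives 1.16 to 1.19.
- Delays of 0.17 and 1.0 years: 0.9227/0.6115 = 1.51 (range 1.49 to 1.54).
- Counted from treatment start: 1.00 in every case.

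**3. One switch direction versus the other (simulation, 1,000,000 patients).** With equal mean switch times the ratio from diagnosis is 1.00. With means of 0.5 and 1.5 years it is about 1.26. Counted from the switch, it is 1.00 in both cases.

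**4. Omitted prognostic factor.** Take a binary factor with hazard ratio h, base hazard 0.2 per year (mean 5 years) and prevalence p. The group rate is expected deaths over expected person-years to 3 years.

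| h | prevalence | rates | ratio |
|---|---|---|---|
| 2 | 40% vs 50% | 0.2681 / 0.2873 | 0.93 |
| 2 | 30% vs 60% | 0.2498 / 0.3075 | 0.81 |
| 3 | 40% vs 50% | 0.3165 / 0.3526 | 0.90 |
| 3 | 30% vs 60% | 0.2836 / 0.3922 | 0.72 |

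This bias does not depend on which switch comparator is meant.

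**The case against.** A reader might infer that both comparisons are bound to suffer immortal-time bias and that a drug or a switch will look protective. The article does not support that.

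- **Drug versus drug.** Both groups are treated, so both must survive to start. Bias needs unequal delays, or switchers classed by their later drug. The article states neither, and it does not say how long after diagnosis treatment begins. This stands.
- **Switch.** The roughly halved ratio belongs to switched versus never switched. The text names no never-switched group, and its two groups can be read as the two switch directions. This stands; the large figure is conditional.
- **Clock.** The origin at diagnosis is attached to the primary endpoint. The secondary list also includes survival on the transplant waitlist, so diagnosis need not be the origin everywhere, and a condensed article may leave such detail to a fuller document. This stands in part: no other definition of LTx-free survival is given, and the matching is expressly anchored at diagnosis.
- **Confounding.** The Statistical analysis section plans a multivariable Cox model, and lung function and 6MWD are among the candidate predictors. Fibrosis extent partly reflects lung function, since CPI was developed against it. But the Cox model is not tied to these comparisons, and fibrosis extent captures neither dyspnea nor exercise capacity. The matching set is stated, not left open, so this point survives. Centre is different: the article treats participating site only as a subgroup factor and does not call it a main predictor.

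**Conclusion.** The concern holds in a limited form. The firm part is the matching: four variables at diagnosis, without the three domains the study itself treats as prognostic, and with no means of balancing disease status at a later start or switch. Residual confounding is likely. Its direction cannot be known in advance; its size under the assumed imbalances is a ratio of 0.93 down to 0.72 where the truth is 1.00.

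The time-origin part is conditional. It is large (about 0.4 to 0.5) only if switched patients are set against non-switched patients from diagnosis. It is moderate (about 1.2 for a 4-month difference in start, about 1.26 for the switch timings assumed) if the groups differ in timing, and absent if they do not. All sizes rest on exponential survival and on assumed switch rates, delays and confounder strengths.

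These are secondary subanalyses. The primary validation of RISE is not affected. The point is a worthwhile, inexpensive improvement.

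**What to change.** - **Drug comparison:** count from first antifibrotic intake and form the groups by first drug received.
- **Switch analysis:** name the comparator. Either count from the switch date against patients still on their first drug at the same time since start, or fit switch as a time-dependent covariate.
- **Adjustment in both:** in addition to the present four variables, adjust for lung function (FVC, DLCO or CPI), 6MWD and MRC dyspnea score at that time zero, and for centre. Where switchers are few, use RISE as a single summary in place of its components.

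The cost is a change of wording: starts and switches are already recorded, and dyspnea, lung function and 6MWD are measured every 4 months. The downsides are slightly shorter follow-up per patient in these comparisons, and a small switch group (a subset of cohorts of 125) that can carry few covariates.
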